### Inclusion and exclusion criteria

2.2

To be included in this study, individuals must meet the following inclusion criteria: (A) inpatient elective or emergency admission to one of the two psychiatric clinics; (B) age over 18 years; (C) sufficient understanding of spoken and written German; (D) primary diagnosis of depression according to ICD-10 (F32 or F33), as diagnosed by a physician or clinical psychologist in conjunction with the M.I.N.I. Screen [Mini-International Neuropsychiatric Interview Screen (57)] and M.I.N.I. [Mini-International Neuropsychiatric Interview (58–60)] diagnostic tools; and (E) informed voluntary consent. Diagnoses are coded according to the International Classification of Diseases (ICD-10-GM) applicable in Germany, both for psychiatric disorders and for non-psychiatric comorbidities. The M.I.N.I., a structured clinical interview, is based on both the Diagnostic and Statistical Manual of Mental Disorders (DSM-V) and the ICD-10-GM. This additional instrument is intended to supplement the diagnostic process, increase diagnostic certainty, and better characterize suicidality and psychiatric comorbidities, with our focus particularly on anxiety disorders. The following exclusion criteria were applied: (a) a current lack of capacity to provide consent (e.g., pronounced psychotic symptoms, stuporous depressive syndrome, and thought constriction to suicidality); (b) previous participation in the study; (c) pregnancy or breastfeeding; and (d) an inpatient stay of less than 7 days, even if the patients initially met the inclusion criteria (post-enrollment exclusion).


As empirical assumptions for the interplay between depression and loneliness in the inpatient and follow-up depression therapy are rare, we decided to set a change of 2 points in the MADRS per 1 SD of loneliness (3-Item UCLA Loneliness Scale) as the minimum meaningful association that shall be detected via the interaction (baseline x change) over the inpatient and post-treatment course. The model tested baseline loneliness and change in loneliness with at least 1.75 points MADRS as we have no empirical assumptions about which association is more significant for this setting, but we have a theoretical assumption that these single associations are less significant than their interaction. An omnibus likelihood ratio test will evaluate these assumptions in a single model, followed by Holm-Bonferroni corrected single tests to evaluate these three assumptions. This step will also evaluate the direction of effects and theoretical plausibility (more loneliness at baseline and less change in loneliness shall predict higher depressive symptom severity). The primary analysis of the linear mixed model includes all three measurement points as a categorial factor. Potential time- effects will serve as covariates in this model and will be reported exploratory with no influence on sample size calculation. Studies examining the clinical course of inpatient depression treatment measured with the MADRS report partly comparable values of MADRS at baseline (≈ 30 points) (62–64) and discharge, though findings remain heterogeneous (65, 66). Model assumptions for this sample size calculation were therefore based on plausible clinical values: T0 = 30, T1 = 16, T2 = 15 MADRS points, with a constant standard deviation of *SD* = 8 across all time points. Between-person differences in depression symptom severity (MADRS) were considered with fixed and random slopes, and ICC was set at .50. Power simulation involved assumptions of approximately 5% missing completely at random (MCAR) and 10% missing at random dropout at T2 (MAR). Sample size estimation was performed with R using the following packages: lme4, lmerTest, MASS and tidyr. The simulation for the overall model yielded a statistical power of ≥ 80% for all three assumptions at *n* = 172 with 15% combined dropout rate (MCAR, MAR), resulting in a total of *n* = 199. The number of simulations was 500 (nsim = 500) at a significance level of *α* = 0.05 for the omnibus likelihood-ratio test, with Holm-Bonferroni corrected single hypothesis tests. As depression can lead to cognitive distortion, correlations between loneliness and depression might be dependent on the measurement point, and given the insufficient clinical validation of the loneliness measures, it remains unclear whether the assumptions of a normal distribution and the assumed level of measurement adequately describe the interplay between depression and loneliness. Additional statistical methods are employed in an explorative and descriptive manner (generalized linear mixed-effects model and mixed analysis of variance). Power-analysis for mixed ANOVA using G*Power Version 3.1.9.7, with categorical groups of ‘high’ and ‘low’ loneliness (median-split) when considering an α error of 0.05, a power of 0.9 (1-β error probability) and a correlation value among repeated measures of 0.5 for the group’s results an estimated sample size of *n* = 36 participants assuming a medium effect size (*f* = 0.25), and *n* = 214 participants assuming a small effect size (*f* = 0.10).

To ensure the external validity of the results, it is important that both severely lonely depressive patients and less lonely depressive patients, as well as different disease trajectories and patient characteristics (e.g., age, sex, and number of comorbidities), can be identified. A sample size of approximately 200 participants is expected to ensure sufficient heterogeneity. This sample size is feasible in practice, since even taking into account an inclusion rate of 50% and a dropout rate of 30% for the primary diagnosis of depression at the University Hospital and the Community Hospital in Erlangen, the recruitment potential significantly exceeds the target number of cases within an estimated period of no more than two years.

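### The total of 199 is not a correct 15% dropout allowance on n = 172, and the plan does not say whether 172 is the enrolled or the evaluable number

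*Protocol article*

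**What the plan says.** All the figures are in Section 2.3 (Sample size consideration) of the protocol article.

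- Missing data: "Power simulation involved assumptions of approximately 5% missing completely at random (MCAR) and 10% missing at random dropout at T2 (MAR").
- Result: the simulation "yielded a statistical power of ≥ 80% for all three assumptions at *n* = 172", and the sentence continues "with 15% combined dropout rate (MCAR, MAR), resulting in a total of *n* = 199".
- Test procedure: 500 simulation runs, "at a significance level of *α* = 0.05 for the omnibus likelihood-ratio test, with Holm-Bonferroni corrected single hypothesis tests".
- Feasibility: the section's last paragraph argues that recruitment at the two hospitals exceeds a target of about 200, "even taking into account an inclusion rate of 50% and a dropout rate of 30" per cent.

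Two other sections bear on how a loss counts. Section 2.6 limits the primary analysis set to participants with MADRS and 3-Item UCLA at T0 and T1; T2 is not required. Section 2.2 removes stays under 7 days after enrolment, and Section 2.6 confirms that these participants are outside the primary set.

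**The concern.** A dropout allowance has one purpose: enrolled number times retained fraction should return the number the power calculation needs. Here 199 does not return 172 at the stated losses.

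The text also supports two readings of 172. If the simulated data sets already contained the 5% and 10% missingness, 172 is the number to enrol and no further inflation is due. If 172 is the number needed after losses, inflation is due and 199 is slightly short. A reader cannot tell which was meant, so cannot tell what power the study has at 199.

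The feasibility paragraph then uses twice the dropout rate without saying what the higher rate describes. At stake is whether a reported design figure can be traced, and whether the 15% is the loss the study team expects. Any shortfall bears on the three Holm-corrected coefficient tests more than on the omnibus test.

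**Working it through.** **Inputs, all from Section 2.3:** base n = 172; combined dropout 15%, made up of about 5% MCAR and 10% MAR at T2; total 199; power at least 80%; 500 runs; feasibility dropout 30%.

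**1. Reproducing 199**

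| Method | Calculation | Total |
|---|---|---|
| Divide by retained fraction, 15% | 172/0.85 = 202.4 | 203 |
| Divide, 5% then 10% | 172/(0.95 × 0.90) = 201.2 | 202 |
| Multiply by 1.15 | 172 × 1.15 = 197.8 | 198 |
| Multiply by 1.05 and 1.10 | 172 × 1.05 × 1.10 = 198.66 | 199 |

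Only the last line gives the printed figure. That it is the source is an inference, since the article shows no formula.

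**2. Does 199 return 172?**

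- 199 × 0.85 = 169.2
- 199 × 0.95 × 0.90 = 170.1
- Largest loss that 199 can absorb: 1 − 172/199 = 13.6%

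So 199 leaves about 2 to 3 fewer than 172, and the total is 3 to 4 below 202 to 203.

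**3. Power if 172 is evaluable**

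Assume power is exactly 80% at 172 and scale the noncentrality by √(n/172). At two-sided α = 0.05 the noncentrality is 1.960 + 0.842 = 2.802. With 169.2 evaluable it becomes 2.802 × √(169.2/172) = 2.779, and power is Φ(2.779 − 1.960) = 79.3%. At α = 0.05/3 the result is 79.2%. The Monte Carlo standard error of an 80% estimate from 500 runs is √(0.8 × 0.2/500) = 1.8 points, so the shortfall is smaller than the simulation's own noise.

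**4. Power if 172 is enrolled**

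The 15% is then already inside the result, which corresponds to 172 × 0.85 = 146.2 effective participants. Enrolling 199 at the same loss rate gives 2.802 × √(199/172) = 3.014 and power Φ(3.014 − 1.960) = 85.4% (86.1% at α = 0.05/3), again starting from exactly 80% at 172. The second inflation is surplus.

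**5. The 30% figure, as a what-if only**

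If 30% of 199 were lost completely, 199 × 0.70 = 139 would remain. Scaling from exactly 80% gives 70 to 71% if 172 is evaluable and about 78% if 172 is enrolled.

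A check simulation used the stated effects ("set a change of 2 points in the MADRS per 1 SD of loneliness" for the interaction, 1.75 for the other two), the stated means, SD 8 and ICC 0.50. It used 1,500 runs, a known covariance matrix, and independent standardised baseline and change. The article does not give the random-slope variance, so a slope SD of 0, 2 or 4 was assumed.

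| Scenario | Single-coefficient power (Holm) |
|---|---|
| 139 complete cases, slope SD 0 | 86–97% |
| 139 complete cases, slope SD 2 | 82–91% |
| 139 complete cases, slope SD 4 | 68–77% |
| 199 enrolled, 25% missing at T2 plus 5% MCAR, slope SD 0 to 4 | 85–99% |

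Omnibus power was at least 98.8% throughout. The slope variance was added on top of SD 8. At slope SD 4 the T2 variance is therefore 64 + 4 × 16 = 128, an SD of 11.3, which departs from the plan's constant SD of 8.

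**The case against.** The strongest defence is that 199 can be derived from the plan's own two components, that it lies within 4 participants (about 2%) of the strict answer, and that the working target is about 200 in any case. The size of the gap is conceded. The method is not: adding 5% and 10% to the base does not restore 172 after losing 5% and 10% of the larger number.

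A second defence is that dividing by the retained fraction treats a participant missing only T2 as wholly lost, whereas Section 2.6 keeps that participant in the mixed model. This is right, and it makes the shortfall in the working an upper limit. It also supports the enrolled reading of 172, under which no inflation was needed.

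A reader might go further and infer from the 30% that only 139 participants will be analysed and that the study has about 70% power. The documents do not support that:

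- The 30% is paired with a 50% inclusion rate in an argument about recruitment potential. It is a cautious margin, and nothing says the enrolled 199 will shrink by it.
- The 70% assumes exactly 80% at 172, where the article says at least 80%. It also assumes that every dropout is lost entirely and that 172 is evaluable.
- The primary test is the omnibus likelihood-ratio test, and no material effect on it has been established.

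What remains of the 30% point is that one section uses the word dropout for two rates, 15% and 30%, without relating them. Losses before T1, including stays under 7 days, do leave the primary set, and the article does not say whether the 15% covers them.

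**Conclusion.** The point holds as an error in a reported design figure, with little effect on power. The total of 199 is not a correct allowance for 15% combined dropout on 172. If 172 is evaluable, the total should read 202 to 203, or about 170 evaluable should be stated; power is then about 79%, provided it is exactly 80% at 172. If 172 is enrolled, with missingness already simulated, 199 counts dropout twice and is conservative, at roughly 85% on the same proviso. The text does not settle which reading applies.

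The 15% and 30% rates need reconciling. That the stated 80% power fails at 30% dropout is not shown.

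**What to change.** 1. State in Section 2.3 whether 172 is the enrolled or the evaluable number, and show the formula behind the total.
2. If evaluable, restate the total as 202 to 203, or keep about 200 and say that about 170 evaluable are expected, with power about 79% if it is exactly 80% at 172.
3. If enrolled, drop the second inflation and restate the power at 199.
4. Say what the 30% refers to (attrition in recruitment, loss before T1, or loss before T2), reconcile it with the 15%, and say whether stays under 7 days are inside the allowance.
5. Only if a 30% loss before T1, short stays included, is considered plausible, re-run the simulation at about 139 analysable participants. Report the result as a sensitivity figure for the Holm-corrected coefficients. Do not state 70% as the study's power.

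The cost is a short text correction and at most one or two re-runs of an existing simulation. Keeping the target at about 200 needs no extra patients; printing 202 to 203 raises the stated total by 3 to 4.

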### Measures

2.4

#### Primary outcomes

2.4.1

To increase the validity of the primary outcome measures and reduce inherent bias for depression, a clinician-rated instrument (Montgomery–Åsberg Depression Rating Scale or MADRS) and a self-report instrument (9-Item Patient Health Questionnaire or PHQ-9) will be employed. However, loneliness is conceptualized as a fundamentally subjective construct. Therefore, we will use the two most established scales (the UCLA Loneliness Scale and De Jong Gierveld van Tilburg Loneliness scales), each in their abbreviated form. To capture the characteristics of the social network as a more objectively accessible domain, an adapted version of the Social Network Indices measure is used within the assessment battery. Furthermore, we administer an additional, newly developed single item intended to capture situational (state) versus enduring (trait) aspects of loneliness. Neither the adapted German Social Network Index nor this single item have been psychometrically validated and therefore cannot be used as established measures. Accordingly, any analyses involving these measures are strictly exploratory, and are not interpreted as validated indicators of objective network size or state versus trait loneliness.

##### Depression

2.4.1.1

###### Montgomery–Åsberg Depression Rating Scale (MADRS)

2.4.1.1.1

Core symptoms of depression will be assessed by using the MADRS (67, 68), which is a widely used semi structured clinician-rated interview consisting of 10 items (*apparent sadness, reported sadness, inner tension, sleep, appetite, concentration, lassitude, inability to feel, pessimistic thoughts, and suicidal thoughts*). Each of these items is rated on a scale from 0 to 6, with a sum score ranging from 0 to 60 points. Higher scores indicate greater severity of depressive symptoms, with scores of 31 or above suggesting the presence of severe depressive syndrome (69). The assessment refers to the preceding seven days and is considered to be suitable for repeated measurements (68, 70).

###### Depression (self-report): 9-Item Patient Health Questionnaire (PHQ-9)

2.4.1.1.2

The PHQ-9 (71, 72) is a self-report measure that is used to assess depressive symptomatology and is frequently used in both clinical and non-clinical populations (73, 74). It comprises nine items reflecting the DSM-IV criteria for major depressive disorder but remains one of the most frequently used self-report measures. The PHQ-9 is rated on a four-point Likert scale (0 = *not at all*, 1 = *on several days*, 2 = *on more than half of the days*, and 3 = *nearly every day*). The sum score ranges from 0 to 27 and is used to evaluate the severity of depressive symptoms. A score of 20 or higher is indicative of severe depressive syndrome. Moreover, scores ≤ 4 denote no or minimal symptoms, scores between 5 and 9 indicate mild symptoms, scores between 10 and 14 indicate moderate symptoms, and scores between 15 and 19 indicate moderately severe depressive symptoms.

##### Loneliness

2.4.1.2

###### 3-Item University of California, Los Angeles (UCLA) Loneliness Scale (3-Item UCLA)

2.4.1.2.1

The 3-Item version (49) is a shortened form of the original 20-Item UCLA Loneliness Scale (75–77) and demonstrates comparable main psychometric criteria (50) and thus benefits regarding secondary test criteria (economy, acceptability). Loneliness is measured through three items, including (1) *feeling a lack of companionship*, (2) *feeling left out*, and (3) *feeling isolated from others*, which are rated on a three-point Likert scale (1 = *hardly ever/never*, 2 = *some of the time*, and 3 = *often*). The resulting sum score (range: 3–9) reflects the degree of perceived loneliness, with higher scores denoting greater loneliness. Cutoff values vary across different studies, although thresholds above 4 or 6 points are most frequently used to classify individuals as ‘lonely’.

###### 6-Item De Jong Gierveld van Tilburg Loneliness Scale (6-Item DJGLS)

2.4.1.2.2

The 6-Item short version, similar to the original 11-Item scale (51), captures two dimensions of loneliness, so-called social and emotional loneliness, but can also be used as a unidimensional measure of overall loneliness. Again, the shorter version was found to have validity and reliability comparable to the longer version (51). Each of the six statements is rated on a three-point scale (1 = *no*, 2 = *more or less*, and 3 = *yes*). Before the total score is calculated, the items are dichotomized, thus resulting in a sum score ranging from 0 to 6, wherein scores of 0–1 indicate no loneliness, 2–4 indicate moderate loneliness, and 5–6 indicate severe loneliness (51). The measure demonstrates good reliability and sufficient content validity (52).

#### Secondary outcomes

2.4.2

##### Social support: Fragebogen zur sozialen Unterstützung, Kurzform (F-SozU-14)

2.4.2.1

Social support is measured with the F-SozU (78), which is a 14-item German short form that demonstrates good reliability (Cronbach’s *α* = 0.80 or higher) and criterion validity. The instrument comprises 14 items assessing instrumental, social, and emotional dimensions of support. Responses are scored on a five-point Likert scale ranging from 0 *(‘does not apply’)* to 4 *(‘applies exactly’)*, with higher total scores indicating higher levels of perceived social support.

##### Social network: adapted social network index (adapted SNI)

2.4.2.2

The Social Network Indices measure (79–81) reflects the degree of social integration or isolation. In the present study, an adapted and German-translated version was used to capture participants’ social interaction partners during the prior two weeks. The German adaption was developed specifically for the present study and represents a newly compiled version, as no German validated version is available, awaiting formal validation. Via the use of a yes/no response format, participants indicated whether they had personal or telephone contact with each of the following: (1) *spouse or partner*, (2) *own children*, (3) *parents or parent-like figures*, (4) *other relatives (e.g., siblings, uncles, or aunts)*, (5) *friends*, (6) *neighbors*, (7) *colleagues*, (8) *people known through voluntary activities*, (9) *in-laws (parents, sons, or daughters-in-law)*, and (10) *members of their social group (e.g., community, congregation, sports, or music clubs)*. In line with the structure and logic of validated English Social Network Indices, higher total scores indicate greater social connectedness. Because this adapted German version has not been formally validated, its scores may be subject to measurement bias (e.g., altered factor structure, item non-equivalence relative to the original instruments, or ceiling effects). Accordingly, all analyses involving the adapted Social Network Index are exploratory and hypothesis-generating, and its results are interpreted descriptively rather than as validated indicator of social network structure.

##### Health status: short form 12 health survey (SF-12)

2.4.2.3

The SF-12 (82–84) captures the health-related quality of life and retains 12 items of the longer SF-36 that represent eight dimensions of physical and mental well-being. The two composite scores (including the physical component summary and mental component summary) are standardized (*M* = 50, *SD* = 10), demonstrate acceptable Cronbach’s *α* > 0.80 and have been validated in various countries and populations. Higher values indicate better health.

##### Quality of life: WHO-five well-being index (WHO-5)

2.4.2.4

The World Health Organization Well-Being Index (WHO-5) (85) is a brief and universally applicable measure of general well-being over the past two weeks. Each of the five items is positively phrased (e.g., *‘I have felt calm and relaxed’*) and rated on a six-point Likert scale (0 = *at no time*, 1 = *some of the time*, 2 = *less than half of the time*, 3 = *more than half of the time*, 4 = *most of the time*, and 5 = *all of the time*). The total score (0–25) is transformed to a scale ranging from 0 to 100, with scores ≤50 indicating diminished well-being.

##### Social anxiety: social phobia inventory (SPIN)

2.4.2.5

The German version of the Social Phobia Inventory (SPIN) (86, 87) is a 17-item self-report measure designed to assess multiple dimensions of social anxiety, including physiological arousal (e.g., ‘*My heart is racing when I am with other people.’*), fear of negative evaluation (e.g., ‘*I am very afraid of being criticized.*’), and avoidance behavior (e.g., ‘*I avoid activities in which I am the center of attention.*’). Responses are scored on a five-point Likert scale (0 = *not at all* and 4 = *extremely*), thereby reflecting the extent of distress associated with each item. The German version also exhibits good psychometric criteria (Cronbach’s *α* = 0.94; test-retest *r* = 0.88).

##### Somatic symptom burden: 13-item somatic symptom severity scale of the patient health questionnaire (PHQ-13)

2.4.2.6

Somatic symptoms will be assessed by using the German version of the Patient Health Questionnaire (72, 88). The psychometric validity of the PHQ-13 is comparable to that of the PHQ-15; however, the former measure enhances usability and gender neutrality. Thirteen physical symptoms are scored over the preceding four weeks, including the degree of associated impairment (0 = *not impaired at all*, 1 = *slightly impaired*, and 2 = *severely impaired*).

##### Inpatient treatment duration

2.4.2.7

The number of days from the beginning of inpatient treatment to the day of discharge from inpatient therapy will be recorded.

#### Other variables

2.4.3

##### Biosampling

2.4.3.1

Biological samples (including blood, saliva, and stool samples) are collected at each assessment point (T0, T1, and T2). Since the analysis of biological samples is exploratory and for hypothesis-generating purposes in this study, we strive to reduce method bias variance by restricting biosampling to the university hospital site to minimize preanalytical errors and ensure procedural consistency. Blood sampling is coordinated with routine clinical blood collections. An additional volume of up to 28.2 ml of venous blood is collected (2 × 9 ml EDTA tubes, 1 × 2.7 ml EDTA tubes, and 1 × 7.5 ml serum tubes). Routine laboratory analyses, including analyses of metabolic markers such as Low-Density-Lipoprotein, High-Density-Lipoprotein, and HbA1c, are performed by the Central Laboratory of the University Hospital Erlangen. The remaining samples are centrifuged, processed (red blood cell lysis for lymphocytes), aliquoted, and stored at -80 °C in the certified biobank (DIN EN ISO 20387) of the University Hospital Erlangen, which is a member of the German Biobank Network. To ensure consistency and comparability of the results of the biochemical analyses, the time between blood collection and the start of processing in the certified biobank is less than two hours. Metabolic, immunological, and hormonal parameters, as well as neurotrophic factors (such as BDNF) are subsequently analyzed by using commercially available antibody-based ELISAs and complementary detection techniques. The activity of enzymes of the sphingolipid metabolism, which are involved in cellular signaling pathways and crucial for maintaining cell membrane structure, will be measured with established assays employing fluorescently labeled substrates (89, 90).

Participants collect saliva samples themselves 30 minutes after awakening (indicating the cortisol awakening response) and a maximum of 30 minutes before bedtime to capture the circadian rhythm of HPA axis activity (91, 92). An evening sample is considered to be a practical surrogate measure of basal HPA axis function, whereas a diurnal nadir typically occurs during nocturnal sleep. All of the saliva samples are collected by using Salivette^®^ (93) and stored at minimum -20 °C in the central biobank of the University Hospital Erlangen until further analysis.

Stool samples are also self-collected by participants by using a collection kit involving a collection tube with stool stabilizer and a feces catcher. Stool samples are stored at -80 °C in the central biobank of the University Hospital Erlangen until subsequent 16S rRNA-based microbiome analysis.

